|----------------------------|-----------------------------------------------------------------------------------------------------------------------------------------------------------------------------------------------------------------------------------------------------------------------------------------------------------------------------------------------------------------------------------------------------------------------------------------------------------------------------------------------------------------------------------------------------------------------------------------------------------------------------------------------------------------------------------------------------------------------------------------------------------------------------------------------------------------------------------------------------------------------------------------------------------------------------------------------------------------------------------------------------------------------------------------------------------------------------------------------------------------------------------------------------------------------------------------------------------------------------------------------------------------------------------------------------------------------------------------------------------------------------------------------------------------------------------------------------------------------------------------------------------------------------------------------------------------------------------------------------------------------------------------------------------------------------------------------------------------------------------------------------------------------------------------------------------------------------------------------------------------------------------------------------------------------------------------------------------------------------------------------------------------------------------------------------------------------------------------------------------------------------------------------------------------------------------------------------------------------------------------------------------------------------------------------------------------------------------------------------------------------------------------------------------------------------------------------------------------------------------------------------------------------------------------------------------------------------------------------------------------------------------------------------------------------------------------------------------------------------------------------------------------------------------------------------------------------------------------------------------------------------------------------------------------------------------------------------------------------------------------------------------------------------------------------------------------------------------------------------------------------------------------------------------------------------------------------------------------------------------------------------------------------------------------------------------------------------------------------------------------------------------------------------------------------------------------------------------------------------------------------------------------|
| Exclusion Criteria: | 
 
• Radiographic or cytologic evidence of leptomeningeal or multicentric disease at any time prior to vaccination.
 
• Prior conventional antitumor therapy other than steroids, RT, or TMZ.
 
• Pregnant or need to breast feed during the study period (Negative <math>\beta</math>-HCG test required).
 
• Requirement for continuous corticosteroids above physiologic levels at time of first vaccination.
 
• Active infection requiring treatment or an unexplained febrile (<math>> 101.5^{\circ}</math> F) illness.
 
• Known immunosuppressive disease or human immunodeficiency virus infection.
 
• Patients with unstable or severe intercurrent medical conditions such as severe heart or lung disease.
 
• Allergic or unable to tolerate TMZ for reasons other than lymphopenia.
 
• Patients with previous inguinal lymph node dissection.
 
• Prior treatment with daclizumab for any reason.
 
• Prior allogeneic solid organ transplant.
 
                                                                                                                                                                                                                                                                                                                                                                                                                                                                                                                                                                                                                                                                                                                                                                                                                                                                                                                                                                                                                                                                                                                                                                                                                                                                                                                                                                                                                                                                                                                                                                                                                                                                                                                                                                                                                                                                                                                                                                                                                                                                                                                                                                                                                                                                                                                                                                                                                          |
| Study Design:       | 
Twenty patients with newly-diagnosed EGFRvIII+ high grade glioma (WHO III or IV) will undergo leukapheresis for immunologic monitoring. Only 1 dose level of daclizumab (1 mg/kg) will be assessed. The decision to dose escalate in subsequent trials will be dependent on analysis of the safety and immunologic responses obtained in this trial. Patients will be followed until death. This study will be halted if any 2 patients experience a drug-related Grade IV or irreversible Grade III toxicity. After initial leukapheresis, all patients will then receive RT and concurrent TMZ at a standard targeted dose of 75 mg/m^2/d. Patients with progressive disease during radiation, dependent on steroid supplements above physiologic levels at time of vaccination, unable to tolerate TMZ or whose PBLs fail to meet release criteria will be replaced, but no more than 40 patients will be enrolled overall. Remaining patients will then receive the initial cycle of TMZ at a targeted dose of 100mg/m^2/d for 21 days <math>3 \pm 1</math> weeks after completing RT and will be independently randomized to receive daclizumab versus saline simultaneous with vaccine #1. An additional cohort of 6 patients (cohort #2) will receive serial administrations of daclizumab at vaccine # 1, vaccine # 3, and during the recovery from each TMZ cycle for the first 3 cycles at the same dose. Vaccine #1 will be given on day <math>21 \pm 2</math> days after the start of the 100mg/m^2/d dose of TMZ. While standard dose 21-day TMZ treatment at a target dose of 100 mg/m^2/day is recommended, TMZ regimen may be adjusted at the discretion of the treating neuro-oncologist. Vaccine will always be given on day <math>21 \pm 2</math> of each 28 day TMZ cycle. Vaccines will be given intradermally and divided equally to both inguinal regions. The calculated dosage of daclizumab will be administered in a 50 mL of sterile 0.9% sodium chloride solution via a peripheral or central vein over a 15 minute period. Vaccine #2 and #3 will occur at 2 week intervals. Patients will then be treated monthly with TMZ cycles for a total of 6 cycles after RT. TMZ will be given on days 1-5 of a 28 day cycle. Subsequent vaccines will be given on day <math>21 \pm 2</math> of each of the five remaining TMZ cycles. Cohort # 2 will receive subsequent vaccinations along with daclizumab (1 mg/Kg) on day <math>21 \pm 2</math> for first 3 cycles. Vaccines will then continue monthly until progression. An additional leukapheresis will be required for any patients who have a positive DTH skin test for PEPvIII for immunologic monitoring. Patients will be imaged after vaccine #4 and then bimonthly without receiving any other prescribed antitumor therapy until progression. Blood work for immunologic monitoring will be drawn before vaccine #1 and then each vaccine after vaccine #3. Blood work for sub-clinical autoimmunity will be drawn before vaccine #1 and every 4 months after vaccine #3. As part of standard care for these patients, upon tumor progression, participants may undergo stereotactic biopsy or resection. As this is not a research procedure consent will be obtained separately. However, if tissue is obtained, it will be used to confirm tumor progression histologically and to assess immunologic cell infiltration and EGFRvIII antigen escape at the tumor site.
 |

# 1 ABSTRACT AND STUDY SCHEMA

## 1.1 Abstract

Malignant primary brain tumors are the most common cause of death among children, and account for more deaths in adults than melanoma(Kotliarov, Steed et al. 2006). This is principally because conventional therapy is severely constrained by the need to eradicate tumor cells that are hidden behind a restrictive blood-brain barrier or that have invaded eloquent brain tissue. As a result, surgery and radiation must be curtailed to avoid incapacitating collateral damage(Imperato, Paleologos et al. 1990), and chemotherapy becomes toxic to rapidly dividing extracerebral normal tissues before eliminating all intracerebral tumor cells. The immune system, however, has the capacity to eliminate altered neoplastic cells with incredible specificity.

A consistent in-frame deletion in the extra-cellular domain of the EGFR produces a constitutively active tyrosine kinase(Batra, Castelino-Prabhu et al. 1995; Chu, Everiss et al. 1997) that enhances neoplastic cell growth and migration(Boockvar, Kapitonov et al. 2003; Pedersen, Tkach et al. 2004) and confers radiation(Lammering, Hewit et al. 2003; Lammering, Hewit et al. 2004; Lammering, Valerie et al. 2004; Li, Yuan et al. 2004) and chemotherapeutic(Montgomery, Guzman et al. 2000; Nagane, Narita et al. 2001) resistance to tumor cells in patients with GBM and a broad array of other common cancers(Garcia de Palazzo, Adams et al. 1993; Moscatello, Holgado-Madruga et al. 1995; Wikstrand, Hale et al. 1995; Olapade-Olaopa, Moscatello et al. 2000; Ge, Gong et al. 2002; Luo, Gong et al. 2003; Okamoto, Kenyon et al. 2003; Aldape, Ballman et al. 2004; Cunningham, Essapen et al. 2005; Heimberger, Hlatky et al. 2005). It also results in a truly tumor-specific target amenable to immunotherapeutic attack. Our multi-institutional Phase II study demonstrates that vaccinations with an EGFRvIII-specific peptide induce T- and B-cell immunity, produce complete radiographic responses in all patients with residual tumor, and universally eliminate EGFRvIII-expressing cells(Heimberger, Hussain et al. 2006; Heimberger, Hussain et al. 2006). Recurrent tumors, however, continue to express wild-type EGFR suggesting that the immune response is specific, but productive intra-molecular cross-priming does not occur. We believe that cross-priming may be hindered by the presence of TRegs.

We have recently shown that TRegs are disproportionately represented within the peripheral blood and tumors of patients with GBM and serve to induce a state of profound, but reversible, immunosuppression(Fecchi, Mitchell et al. 2006). TRegs are characterized by constitutive expression of the high affinity IL-2 receptor (IL-2R $\alpha$ )(CD25) and are absolutely and uniquely dependent on IL-2R $\alpha$  signaling for their function and survival(Malek 2003; Malek and Bayer 2004; D'Cruz and Klein 2005; Fontenot, Rasmussen et al. 2005; Maloy and Powrie 2005; Fecchi, Sweeney et al. 2006). Using our spontaneous murine glioma model, we have already demonstrated that pre-treatment with an antibody that blocks IL-2R $\alpha$  signaling and functionally inactivates TRegs without inducing autoimmune toxicity(Fecchi, Ochiai et al. 2006; Fecchi, Sweeney et al. 2006). Established immune responses may also depend on IL-2 signaling of effector T-cells or a novel subset of CD3+CD56bright NK cells(Bielekova, Richert et al. 2004; Li, Lim et al. 2005; Bielekova, Catalfamo et al. 2006), however, such that blocking IL-2R $\alpha$  signaling during ongoing immune responses may impair effector T-cell responses as well(Williams, Tyznik et al. 2006). After periods of lymphopenia, however, physiologic surges in IL-7(Seddon, Tomlinson et al. 2003; Seddon and Zamoyska 2003) and IL-15(Nishimura, Tagaya et al. 2001) drive homeostatic reconstitution of the effector T-cell

compartment and may bypass the need and effects of IL-2 signaling in these cells (Willerford, Chen et al. 1995; Baan, Boelaars-van Haperen et al. 2001).

We have recently shown that TMZ, an alkylating agent that produces a survival benefit in patients with GBM (Stupp, Mason et al. 2005), induces a profound, but transient lymphopenic environment in humans and mice. Our preliminary studies have shown that unarmed CD25-specific antibodies given *in vivo* to mice during recovery from TMZ-induced lymphopenia and in *in vitro* human studies are capable of functionally inactivating TRegs while dramatically enhancing vaccine-induced immune responses. Although others have used recombinant toxins conjugated to IL-2 to deplete TRegs, results have been variable. This may be due to counterproductive direct IL-2 signaling of TRegs, depletion of effector memory cells through constitutively expressed lower affinity IL-2Rs, rapid clearance of the foreign toxin, or depletion of activated T-cells that also transiently express CD25. Conversely, *daclizumab*, an existing humanized unarmed CD25-specific antibody, functions identically to the antibody used for TReg inactivation studies in mice by blocking IL-2 signaling which is critical only to TReg function and survival during lymphopenic recovery.

We hypothesize that *daclizumab* therapy during the recovery from therapeutic TMZ-induced lymphopenia in patients with newly-diagnosed high grade glioma will inhibit the functional recovery of TRegs, enhance vaccine-induced immune responses, and promote cross-priming without the induction of deleterious autoimmunity.

In this protocol, we will determine if *daclizumab* inhibits the functional recovery of TRegs after therapeutic TMZ-induced lymphopenia in the context of vaccinating adult patients with newly-diagnosed high grade gliomas using a tumor-specific, EGFRvIII-targeted peptide vaccine.

## 1.2 Study Schema

[figure not shown]

## 2 HYPOTHESES AND OBJECTIVES

### 2.1 Hypotheses

- Our primary hypothesis is that:
  - Daclizumab will inhibit the functional and quantitative recovery of TRegs in patients with newly-diagnosed high grade glioma during homeostatic proliferation after therapeutic TMZ-induced lymphopenia.
- Secondary hypotheses that will be explored in this study are that:
  - Daclizumab will be safe in combination with CDX-110 in patients with newly-diagnosed high grade glioma during recovery from TMZ-induced lymphopenia.
  - The magnitude and character of humoral and cellular CD8+ and CD4+, EGFRvIII-specific T cell responses will be enhanced in adult patients with newly-diagnosed high grade glioma treated during recovery from TMZ-induced lymphopenia when daclizumab is given during the T cell recovery phase.
  - Daclizumab will not enhance antigen-specific or generalized activation-induced cell death or induce immunologic or clinical evidence of autoimmunity.
  - Daclizumab will alter the phenotype (CD56-expression), cytokine secretion profile, or cytotoxicity of CD3-CD56+ NK cells.
  - Treatment of adult patients with newly-diagnosed high grade glioma using CDX-110 during recovery from TMZ-induced lymphopenia with or without daclizumab will ultimately produce evidence of a prolonged time to progression (TTP) and overall increase in median survival in these patients compared to a matched historical cohort from MD Anderson Cancer Center (provided by [name]).

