### **2.2.2      Secondary Objectives**

- To evaluate the safety of daclizumab in the context of vaccinating adult patients with newly-diagnosed high grade gliomas using CDX-110 during recovery from therapeutic TMZ-induced lymphopenia.
- To determine if daclizumab enhances the magnitude or character of CDX-110-induced cellular or humoral immune responses, inhibits or enhances activation-induced cell death, or induces immunologic or clinical evidence of autoimmunity.
- To determine if daclizumab alters the phenotype (CD56-expression), cytokine secretion profile, or cytotoxicity of CD3-CD56+ NK cells.
- To determine if daclizumab in addition to vaccination extends progression free survival compared to historical cohorts.
- To characterize immunologic cell infiltrate in recurrent tumors and seek evidence of antigen escape outgrowth.

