### **8.1.1 Overview of Statistical Analysis**

Our laboratory and the HVTN Immunologic Monitoring Reference Laboratory, headed by [name] also at Duke University, has devoted considerable effort to co-developing and co-validating the immunologic assays outlined below for monitoring  $T_{Reg}$  function, antigen-specific responses in CD8+ or CD4+ T-cells, and NK cell functional activity in cancer patients. The reproducibility of these assays in our hands ensures that they can be reliably used for monitoring of changes after vaccination with and without daclizumab. Power calculations for this study are based on our primary endpoint which is functional suppressive capacity of CD4+CD25+CD127-  $T_{Regs}$ . For these calculations, we assumed that measurements made in each treatment group at a given phytohemagglutinin (PHA) level would be normally distributed with standard deviation of  $\sigma$ . Based on our experience with these assays within this patient population (Fecci, Mitchell et al. 2006), we estimate that with a sample size of 20 randomized patients we will have 80% power to detect a difference of 1.41  $\sigma$  at the 0.017 significance level (one-tailed). A 0.017 level of significance is used to adjust (Bonferroni correction) for the use of 3 non-zero PHA doses (0.1, 1, 10  $\mu$ g/well) in the proliferation assay. Thus, with only 20 patients, we will have sufficient power to detect treatment effects much more subtle than the ones observed in our pre-clinical studies (Fecci, Sweeney et al. 2006) and effects that we believe would be clinically significant. However, because the magnitude and variability of the effects of daclizumab on  $T_{Regs}$  remain unknown in humans, once human data become available from these studies, power analyses will be recalculated and patient numbers adjusted if needed. If daclizumab treatment does not significantly inhibit the functional recovery of  $T_{Regs}$  (primary endpoint), we would not be interested in the further development of this drug as

a vaccine adjuvant. Therefore, a one-sided hypothesis test is utilized. Power calculations are not provided for subsequent analyses as the number of patients in this trial will be determined by the primary endpoint, and the remainder of the analyses is exploratory and hypothesis generating only. With 10 patients in each arm, however, we will have 80% power to detect difference  $>1.325\sigma$  between groups for each assay at  $\alpha=0.05$ .

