
### **8.2.1 Statistical Analysis**

Our primary endpoint analysis will consist of a comparison of proliferative T-cell response to PHA among treatment groups (+/- daclizumab) using a generalized linear model for normal data that accounts for correlation of measurement replication across PHA doses (0, 0.1, 1, 10  $\mu\text{g/well}$ ) within subjects. This analysis determines whether the difference in treatment groups relative to proliferative response remains constant over 4 PHA doses (i.e. curves remain parallel or not). A test of interaction with 3 degrees of freedom will be used. If the curves deviate significantly from parallelism, we will conclude that the effect of treatment varies as a function of PHA dose level. Within the

context of this model, statistical contrasts will be used to assess treatment differences at specific PHA dose levels. If the test for interaction is not statistically significant, one will conclude that the treatment effect is constant over PHA dose levels. A generalized linear model without an interaction will be used to assess whether the main effect for treatment is statistically significant (i.e. treatment differences are non-zero). In this analysis and others, if assumptions required for t-tests are not satisfied, a non-parametric Wilcoxon rank sum test will be conducted at each PHA level. Significance for this and other assays will be taken at the  $\alpha=0.05$  level unless otherwise indicated. A Bonferroni correction will be used to control for the multiple comparisons.

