#### **8.4.1 Statistical Analysis**

A two-sided t-test will be used to compare cytokine differences between treatment groups as described above.

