### **8.6.1 Statistical Analysis**

All data will be background subtracted and compared between treatment groups using unpaired t-tests as described above..

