### **8.11.1 Statistical Analysis**

For laboratory screening tests of autoimmunity, any change from a normal to an abnormal value or a 2 fold change will be considered a positive result. A patient with any “positive” test will be considered positive and the number of positive tests will not be weighted. A 2 x 2 table will then be constructed to differentiate the frequency of positive patients by treatment group. A  $\chi^2$  test will then be used to assess if these frequencies are statistically significant.

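### An exploratory hypothesis of no increase in cell death or autoimmunity is matched, for cell death and laboratory autoimmunity, only with 10-versus-10 difference tests, which cannot support absence

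*Protocol*

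**What the plan says.** Section 2.1 introduces its secondary list with "Secondary hypotheses that will be explored in this study are that". One item is "Daclizumab will not enhance antigen-specific or generalized activation-induced cell death or induce immunologic or clinical evidence of autoimmunity". The matching objective in 2.2.2 leaves the direction open: whether daclizumab "inhibits or enhances activation-induced cell death, or induces immunologic or clinical evidence of autoimmunity".

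The analyses named are:

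- **Cell death (8.6.1):** data are "compared between treatment groups using unpaired t-tests as described above".
- **Laboratory autoimmunity (8.11.1):** a patient with any positive test on the panel counts as positive. The arms are set out in a 2 x 2 table, and a chi-square "test will then be used to assess if these frequencies are statistically significant".

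Section 8.2.1 sets the level for assays generally: "Significance for this and other assays will be taken at the" 0.05 level unless otherwise indicated. Section 8.1.1 calls all non-primary analyses exploratory and states their sensitivity: "With 10 patients in each arm, however, we will have 80% power to detect difference" above 1.325 SD at 0.05. Neither 8.6.1 nor 8.11.1 gives an interval, a bound or a margin.

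**The concern.** A hypothesis that something will not increase cannot be confirmed by a test built to find an increase. With the tests named, the only agreeing result is failure to reject, and with 10 per arm that result is common even when the increase is real and sizeable.

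The endpoints matter to the protocol's own argument. Section 3.6 asks for particular attention to autoimmune manifestations under this approach. Loss of activated T cells would undercut the reason for giving daclizumab as a vaccine adjuvant. Section 5.1.1 makes dose escalation in later trials depend on the safety and immunologic responses seen here. A bare non-significant p-value would tell those planning the next trial little about how large an increase remains possible.

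**Working it through.** **Inputs.** 10 per arm and 1.325 SD (8.1.1); alpha 0.05 (8.1.1, 8.2.1); unpaired t-test (8.6.1); chi-square test (8.11.1). Section 8.6.1 does not state sidedness. Section 8.4.1 does for cytokines: "A two-sided t-test will be used to compare cytokine differences between treatment groups as described above". The protocol gives no expected rates for the autoimmunity panel, so the rates below are assumptions shown as a range.

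**Reproducing the protocol's figure.** For a true difference of d SD the t statistic has 18 df, noncentrality d × √(10/2) and two-sided critical value 2.101. At d = 1.325 the noncentrality is 2.963 and the power is 80.0%, so the stated figure is correct and two-sided. A one-sided test would give 1.156 SD instead.

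**Cell death, same formula.**

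| True increase | Noncentrality | Power | Missed |
|---|---|---|---|
| 0.5 SD | 1.118 | 18.5% | 81% |
| 0.8 SD | 1.789 | 39.5% | 60% |
| 1.0 SD | 2.236 | 56.2% | 44% |
| 1.325 SD | 2.963 | 80.0% | 20% |

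Power passes 50% at about 0.93 SD. If the test were one-sided, power at 0.5, 0.8 and 1.0 SD would be 28%, 53% and 69%.

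**Laboratory autoimmunity.** All 11 × 11 outcomes for 10 versus 10 were enumerated, summing the binomial probabilities of tables with p ≤ 0.05. The statistic is the uncorrected Pearson chi-square, (difference in proportions)² / [p̄(1 − p̄) × 2/10], where p̄ is the pooled proportion.

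| Assumed saline vs daclizumab | Power | Missed |
|---|---|---|
| 0% vs 20% | 12% | 88% |
| 0% vs 30% | 35% | 65% |
| 10% vs 40% | 29% | 71% |
| 30% vs 70% | 42% | 58% |
| 10% vs 60% | 66% | 34% |

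With a Yates correction or Fisher's exact test, power falls further: 15% for 10% versus 40%, 24% for 30% versus 70%, and 47% for 10% versus 60%.

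The saline rate may not be low, because one positive among 11 laboratory tests is enough. If each test independently had an assumed 5% chance of being positive, 1 − 0.95^11 = 43% of saline patients would count. Power for 43% versus 80% is 37%.

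**What the test leaves unsaid.** Suppose 1 of 10 saline and 5 of 10 daclizumab patients are positive. Then p̄ = 0.30 and the statistic is 0.16 / (0.30 × 0.70 × 0.2) = 3.81, p = 0.051. For 0 of 10 versus 3 of 10, p̄ = 0.15 and the statistic is 0.09 / (0.15 × 0.85 × 0.2) = 3.53, p = 0.060. Both are non-significant. The one-sided 95% upper bounds on the increase (Newcombe score) are about 64 and 56 percentage points.

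For cell death, a one-sided 95% bound lies 1.734 × √(2/10) = 0.78 SD above the observed difference.

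**The case against.** The other side has four good arguments.

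- **Exploratory status.** Section 2.1 says the secondary hypotheses will be explored, and 8.1.1 calls the non-primary analyses hypothesis generating and discloses the 1.325 SD limit. This stands and lowers the weight of the point. It does not make a difference test able to support absence, and an estimate with a bound suits exploratory work better.
- **No stated inference.** A reader might infer that the trial will declare no harm after a non-significant test. The documents do not say so for these endpoints, and the objective in 2.2.2 is neutral. The nearest wording is in 10.3, where the absence of a significant reduction is a condition for further evaluation, but that concerns TTP and survival.
- **Other safety provisions.** A reader might infer that the whole hypothesis rests on these two tests. It does not. Clinical autoimmunity is also followed through adverse-event recording (5.4), DLT definitions and closure rules (5.3.1, 5.3.2) and the arm-specific halting rules in 10.2. Those rules do not estimate a between-arm difference in cell death or laboratory markers.
- **Large effects.** A reader might infer that large harms are missed most of the time. That depends on what counts as large: a 1 SD shift and 10% versus 60% are each detected more often than not.

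Interval reporting is often left to the SAP, which is not at hand. Here, however, the protocol itself names the test, and its hypothesis is worded as absence.

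**Conclusion.** The point holds as a mismatch between wording and method. It is limited to cell death and laboratory autoimmunity and is of modest weight, because both are secondary and declared exploratory. The named tests cannot support a hypothesis of no increase with 10 per arm.

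The miss rates for cell death rest on normal data and a two-sided t-test, the reading that reproduces the protocol's own figure. Those for autoimmunity rest on assumed rates and the uncorrected chi-square test. The point does not show that the trial will claim safety wrongly, nor that clinical autoimmunity goes unwatched.

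**What to change.** In 8.6.1 and 8.11.1, make the main result the daclizumab-minus-saline difference with a one-sided 95% upper bound: t-based for cell death, score-based or exact for the proportion of positive patients. Add that a non-significant test is not evidence of no increase, and that the result will be reported as 'an increase up to [bound] is not excluded'. The tests may stay as supporting results.

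No formal non-inferiority margin is needed. At one-sided 0.025 and 80% power, excluding an assumed margin of even 1.0 SD would take 16 per arm, and 0.5 SD would take 63, against the 10 available.

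The cost is the wording of two paragraphs, with no new data or patients. The downside is that the bounds will be wide, so the trial will usually be unable to claim absence of harm on these endpoints.
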